**Discussion:**

The study aims to provide comprehensive evidence on the clinical effectiveness, cost-effectiveness, and implementation process of IoT-based hypertension management in primary care. By combining quantitative and qualitative methods, it seeks to understand how the intervention works in real-world settings and identify facilitators and barriers to its implementation. The findings could inform policy decisions and optimize resource allocation for chronic disease management in primary care.

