### Objectives

The general aim of this study is to evaluate the effectiveness, cost-effectiveness, and implementation process of an IoT-based hypertension surveillance system in primary healthcare settings in China. Specifically, the study addresses the following research questions:

Clinical Effectiveness: ①What are the effects of the IoT-based monitoring system on blood pressure control rates and standardized management rates compared to traditional care?②Does the intervention improve secondary outcomes, including referral rates for refractory hypertension and biomarker profiles (e.g., lipids, glucose)?Economic Evaluation: What are the incremental costs and cost-effectiveness of the IoT system versus standard care?Implementation Process: What are the facilitators and barriers to deploying the IoT system in routine primary care, as perceived by healthcare providers and patients?

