### Outcomes and variables

The primary outcome of the trial is blood pressure control rate, which is the proportion of patients whose blood pressure is maintained within the target range. According to the National Basic Public Health Service Specification (Third Edition) [15], blood pressure should be controlled below 140/90 mmHg for individuals aged 35–65 years, and below 150/90 mmHg for those aged 65 years and above. Secondary outcomes: (1) standardized management rate: Calculated as the proportion of patients in the intervention and control groups who receive management in accordance with the National Basic Public Health Service Specification (Third Edition) [15], to evaluate the impact of the system on the standardization of hypertension management; (2) blood pressure measurement completion rate: The number of blood pressure measurements completed per patient compared to the expected quarterly measurements; (3) Referral rates: The number of patients referred to higher-level hospitals due to refractory or secondary hypertension, and the proportion of referred patients whose blood pressure stabilizes upon return; (4) Biochemical indicators: Changes in lipid profiles and other relevant biomarkers.

In addition, exploratory outcomes are economic evaluation(cost-effectiveness: analysis of system deployment costs versus improvements in hypertension control and reduced referrals; performance incentives: correlation between system-generated data and family doctor contract fulfillment metrics for incentive allocation), patient satisfaction (the subjective experiences and perceived effects), implementation barriers (engage professionals in focus groups and interviews to examine implementation barriers and improvement opportunities from the service providers’ perspective).

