### Statistical analysis

Statistical analysis will be performed using SPSS 27.0. Normality of continuous variables (e.g., blood pressure values, biochemical indicators) will be assessed using Shapiro-Wilk tests. Normally distributed data will be presented as mean ± standard deviation (x̄ ± s) and analyzed with independent t-tests for between-group comparisons (intervention vs. control) and paired t-tests for within-group changes (baseline vs. follow-up). Non-normally distributed data will be reported as median (interquartile range) and analyzed using Mann-Whitney U test. Categorical variables will be expressed as counts (%) and compared via the chi-square test. A two-sided p-value < 0.05 will indicate statistical significance.

Intention-to-treat analysis will be prioritized [19], with multiple imputation for missing data. Subgroup analyses will be performed for age, hypertension severity, and comorbidity status. In addition, insights on implementation barriers and improvement strategies derived from focus groups and interviews with healthcare professionals will be systematically analyzed using thematic analysis.

The economic evaluation is integrated into the quasi-experimental trial design, comparing the IoT-based hypertension surveillance system (intervention group, IG) with standard care (control group, CG). Costs and outcomes are assessed over a 12-month period to determine incremental cost-effectiveness. The analytical method is Incremental Cost-Effectiveness Ratio (ICER) [20], which is calculated using the following method. Where: ΔC = Change in mean costs (intervention vs. control). ΔE = Change in mean effectiveness (e.g., blood pressure control rate). Bootstrap simulation with 1,000 replications will be conducted to generate ICER distributions, plotted graphically on cost-effectiveness planes.$$\:ICER=\frac{\left({\Delta\:}{C}_{IG}-{\Delta\:}{C}_{CG}\right)}{\left({\Delta\:}{E}_{IG}-{\Delta\:}{E}_{CG}\right)}$$

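### The economic analysis summarises uncertainty as a distribution of ICERs, which becomes unreadable if the control-rate gain is well below the planned 10 points; net benefit from the same bootstrap pairs avoids this

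*Protocol article*

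**What the plan says.** The economic paragraphs of Statistical analysis commit to one measure: "The analytical method is Incremental Cost-Effectiveness Ratio (ICER) [20], which is calculated using the following method". The numerator is defined as "ΔC = Change in mean costs (intervention vs. control") and the denominator as "ΔE = Change in mean effectiveness (e.g., blood pressure control rate"), so the control rate is given only as an example of the effect. The stated purpose is firm: "Costs and outcomes are assessed over a 12-month period to determine incremental cost-effectiveness". Uncertainty is handled in one sentence: "Bootstrap simulation with 1,000 replications will be conducted to generate ICER distributions, plotted graphically on cost-effectiveness planes".

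Objectives makes this a research question: "What are the incremental costs and cost-effectiveness of the IoT system versus standard care". Outcomes and variables ranks it lower: "exploratory outcomes are economic evaluation(cost-effectiveness: analysis of system deployment costs versus improvements in hypertension control and reduced referrals". The abstract says of the study as a whole: "The findings could inform policy decisions and optimize resource allocation for chronic disease management in primary care".

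The article names no net benefit, no acceptability curve and no value per additional controlled patient. The Background mentions a per-capita investment figure of $116 and a Japanese threshold for another product, but adopts neither as a criterion.

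**The concern.** The ICER is not ordered across the four quadrants of cost and effect. A negative value can mean cheaper and better, or dearer and worse. A positive value can mean paying more for a gain, or saving money by losing effect. When replicates of the effect difference lie on both sides of zero, the ratio passes through plus and minus infinity. A mean, percentile or histogram of it then has no consistent meaning.

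The sentence also merges two objects. A cost-effectiveness plane plots pairs of cost and effect differences, not ratios.

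The article gives reasons why the effect could fall short of plan. The Sample size calculation section acknowledges considerable heterogeneity in the meta-analysis behind the 10-point assumption, and the Discussion acknowledges selection bias and unmeasured confounding. The sign of the cost difference is open too: devices and software cost money, while the plan expects fewer referrals. If the gain were small, a numerical summary of the ICER distribution would not answer the economic research question.

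**Working it through.** **Inputs from the article.** Control rates of 45% and 55%, 1,000 patients per group and 15% attrition (Sample size calculation), giving 1,000 × 0.85 = 850 evaluable per group. The intervention is deployed in five family doctor teams (Overall study design and setting). There are 1,000 bootstrap replications (Statistical analysis).

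**Inputs assumed, because the article gives none.** Costs, in arbitrary money units, and the within-team correlation (ICC). Five equal teams are assumed in each group, although the article gives the number of teams for the intervention group only.

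**The plan's own figures.** The economic section contains no computed figure to reproduce. The effect in the ICER denominator comes from the sample size section. Its minimum of 350 per group does not reproduce for 45% versus 55%: the standard two-sided formula gives 392, and power at 350 is 75.5%. The attrition step does reproduce: 350 / 0.85 = 412. This has no bearing here, because 1,000 per group gives 99% power under independence.

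**Step 1: share of replicates at or below zero effect.** If the observed gain is d, the share is Φ(−d/SE), with SE = √[(0.45 × 0.55 + (0.45 + d)(0.55 − d)) / n]. With n = 850 and d = 0.03, SE = √[(0.2475 + 0.2496)/850] = 0.0242 and Φ(−1.24) = 10.7%.

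| Observed gain | n = 850 | n = 1,000 |
|---|---|---|
| 10 points | 0.002% | 0.0003% |
| 5 points | 1.9% | 1.2% |
| 3 points | 10.7% | 8.9% |
| 2 points | 20.4% | 18.5% |

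**Step 2: clustering.** The variance is multiplied by 1 + (m − 1) × ICC, where m is the number of patients per team. With m = 200 (n = 1,000) and ICC 0.02 this is 1 + 199 × 0.02 = 4.98.

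| Observed gain | ICC 0.01 | ICC 0.02 | ICC 0.05 |
|---|---|---|---|
| 10 points | 0.5% | 2.2% | 8.7% |
| 5 points | 9.7% | 15.7% | 24.9% |

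These shares appear in the bootstrap only if teams, not single patients, are resampled.

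**Step 3: what the ratio does.** One thousand bootstrap replicates were drawn at n = 1,000 per group, with an assumed extra cost of 50 and a cost SD of 200.

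| Observed gain | 2.5 to 97.5 percentiles of the ICER |
|---|---|
| 10 points | 275 to 969 |
| 5 points | 455 to 4,723 |
| 3 points | −6,780 to 13,970 |
| 2 points | −14,501 to 15,825 |

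The first is usable. The last two cannot be read as intervals: the replicates that gave the negative values do not lie below the point estimate in any useful sense.

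**Step 4: mixing of quadrants.** This depends on the cost assumption. With an extra cost of 20, a cost SD of 1,000 and n = 850, the SE of the cost difference is 1,000 × √(2/850) = 48.5, so P(dearer) = Φ(20/48.5) = 0.66. At a 2-point gain P(better) = 0.796. If cost and effect are independent, the split is:
- dearer and better: 0.66 × 0.796 = 53%
- cheaper and better: 0.34 × 0.796 = 27%
- dearer and worse: 0.66 × 0.204 = 13%
- cheaper and worse: 0.34 × 0.204 = 7%

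With the Step 3 costs the SE is 200 × √(2/1,000) = 8.94, and 50/8.94 = 5.6, so practically every replicate is dearer. Negative values then mean only dearer and worse, but the ratio is still unbounded near zero effect.

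**Step 5: the alternative.** Incremental net benefit at a value λ per additional controlled patient is λ × (effect difference) − (cost difference). With the Step 3 costs, a 3-point gain and λ = 2,000, it is 2,000 × 0.03 − 50 = 10. Its SE is √[(2,000 × 0.0223)² + 8.94²] = 45.5, so the 95% CI is about −79 to 99. The probability of a positive net benefit is Φ(10/45.5) = 0.59, against 0.58 in the bootstrap. Over λ = 500 / 1,000 / 2,000 / 4,000 the bootstrap probabilities are 0.01 / 0.21 / 0.58 / 0.80 at 3 points and 0.53 / 0.98 / 1.00 / 1.00 at 10 points. The measure is defined at every effect size.

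**The case against.** The strongest reply is that the plan promises no percentile, interval or decision rule for the ICER. It says that the replicates are plotted on the plane, which is the display that keeps the quadrants apart, so the reference to ICER distributions may be loose wording for cost-effect pairs. This largely stands: the intervals in Step 3 are a summary supplied for this check, not one that the plan states. What remains is that the text names the ratio as the method and as the thing whose distribution is generated, and names no other way to express uncertainty.

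A second reply is that a value per controlled patient and an acceptability curve are details that a condensed article may leave to a fuller plan. This stands too, and their absence alone is not counted as an error.

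A reader might go further and infer that cost-effectiveness cannot be determined at all under this plan. The documents do not support that. Dominance can be read from the plane without any threshold, readers can set the point ICER against a value of their own, and at the planned effect the ratio behaves well. Only a verdict in the quadrants that trade cost against effect needs a stated value.

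Finally, the numbers in Steps 2 to 5 depend on assumed costs, ICC and team structure. Step 4 shows that the mixing of opposite meanings can vanish under other costs. Step 1 uses only the article's own figures and a range of gains.

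**Conclusion.** The point holds in a limited, conditional form. As worded, the plan makes the ICER its sole cost-effectiveness measure and describes the bootstrap output as a distribution of that ratio. At the planned 10-point gain with independent patients practically no replicate crosses zero, and nothing is lost. At about 3 points or less, roughly 9% to 20% of replicates do so with 850 to 1,000 independent patients per group and gains of 3 to 2 points. Under assumed ICCs of 0.01 to 0.05 a similar share (10% to 25%) arises already at 5 points, provided that the resampling follows teams. Any numerical summary of the ratio is then unbounded and, depending on costs that the article does not give, may pool opposite meanings. Because the outcome is exploratory and the plane is kept, this is a minor improvement and not a flaw that invalidates the economic evaluation.

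**What to change.** In Statistical analysis, describe the 1,000 replicates as pairs of cost difference and effect difference. Keep the plane and the point ICER, and state that uncertainty will not be summarised by the distribution of the ICER. From the same pairs, report incremental net benefit with a 95% CI and a cost-effectiveness acceptability curve, both over a stated range of values per additional controlled patient. Covariate-adjusted net-benefit regression is an option, not a requirement.

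The change affects wording and reporting only and needs no new data. Its one real cost is that the sponsor must state the range of values, preferably before results are seen, because the conclusion depends strongly on it.

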### Process evaluation

Besides the survey data gathered in the trial, qualitative data will also be collected to assess the intervention process. Qualitative data will be collected through questionnaire surveys with 2000 hypertension patients and focus groups with 12 healthcare providers (doctors, nurses, and administrators) to explore implementation barriers, user experiences, and perceived effectiveness.

### Ethics

The research is conducted in accordance with the ethical guidelines and the Helsinki Declaration. Ethical considerations are prioritized throughout all phases of the study, including recruitment, data collection, storage, analysis, and reporting. Participation in the research is entirely voluntary, and all participants are provided with detailed information about the study objectives, procedures, and potential risks and benefits during the recruitment phase. Written informed consent is obtained from each participant prior to enrollment, ensuring their understanding and agreement to participate in all aspects of the study. Throughout the study, participants are encouraged to contact the research team with any questions or concerns. Data collection is carried out with respect for participant privacy and confidentiality, and all reports and publications will anonymize participant identities to prevent disclosure of personal information.

The research protocol has undergone comprehensive review and obtained approval from the Ethics Committee of Beijing Luhe Hospital, Capital Medical University (Approval No. 2024-LHKY-044-02), ensuring compliance with ethical standards for clinical research in primary healthcare settings. The study protocol has been registered, and all procedures align with the ethical principles of beneficence, non-maleficence, and respect for participant autonomy. Any modifications to the study protocol will be submitted for further ethical review and approval as necessary.

## Discussion

This study represents one of the first attempts to evaluate the effectiveness of an IoT-based hypertension surveillance system in primary healthcare settings in China. The integration of real-time monitoring, automated data analysis, and dynamic performance evaluation tools addresses critical gaps in traditional hypertension management, such as fragmented data collection and low patient adherence. By combining quantitative outcomes (e.g., blood pressure control rates) with qualitative insights from patients and healthcare providers, the study offers a comprehensive understanding of the system’s feasibility and impact.

A key strength of this study lies in its pragmatic quasi-experimental design, which reflects real-world conditions by evaluating an existing intervention within routine clinical practice. The large sample size (*n* = 2000) and rigorous baseline matching enhance the generalizability of the findings to similar urban and suburban primary care settings. Additionally, the inclusion of cost-effectiveness analysis provides valuable evidence for policymakers to allocate resources efficiently.

However, several limitations should be acknowledged. First, the non-randomized allocation of participants (due to the pre-existing deployment of the IoT system in selected locations) may introduce selection bias. Although baseline matching will be used to mitigate confounding, unmeasured variables (e.g., socioeconomic status) could influence outcomes. In addition, the study’s reliance on electronic health records for control group data may lead to inconsistencies in data quality compared to the IoT system’s automated measurements.

### Implications

This study provides critical evidence on the effectiveness and implementation of an IoT-based hypertension surveillance system in primary care settings. By integrating technology with traditional healthcare delivery, the intervention demonstrates potential to significantly improve hypertension control rates and standardize care practices, particularly in resource-limited areas. For clinical practice, the real-time monitoring system enables timely interventions while empowering patients through enhanced self-management capabilities. The study’s mixed-methods approach [21] establishes a valuable framework for evaluating technology-driven health interventions, with findings that could guide wider adoption of similar systems for chronic disease management. Ultimately, this research contributes to advancing healthcare quality and operational efficiency through innovative digital solutions.

## Data Availability

Not applicable.
